**Table 2.7.4-12**      **Summary of AST values (U/L) by treatment and time point**  
**Paediatric safety population**

*Programming note: Same layout as Table 2.7.4-11 for AST*

**Table 2.7.4-13**      **Summary of total bilirubin values (umol/L) by treatment and time point**  
**Paediatric safety population**

*Programming note: Same layout as Table 2.7.4-11 for total bilirubin*

**Table 2.7.4-14**      **Summary of alkaline phosphatase values (U/L) by treatment and time point**  
**Paediatric safety population**

*Programming note: Same layout as Table 2.7.4-11 for alkaline phosphatase*

**Table 2.7.4-15**      **Summary of serum creatinine values (umol/L) by treatment and time point**  
**Paediatric safety population**

*Programming note: Same layout as Table 2.7.4-11 for serum creatinine*

**Table 2.7.4-16**      **Incidence of ALT values relative to the normal range by treatment and time point**  
**Paediatric safety population**  
**(Page 1 of n)**

| Time point                   |                             | Pyronaridine
artesunate
(N=xxx)
n / total (%) | Artemether
lumefantrine
(N=xxx)
n / total (%) | p-value |
|------------------------------|-----------------------------|--------------------------------------------------------|--------------------------------------------------------|---------|
| Day 0                        | ALT ≤1.5 x ULN              | xx / xxx (xx.x)                                        | xx / xxx (xx.x)                                        | 0.xxxx  |
|                              | ALT >1.5 x ULN and ≤3 x ULN | xx / xxx (xx.x)                                        | xx / xxx (xx.x)                                        |         |
|                              | ALT >3 x ULN and ≤5 x ULN   | xx / xxx (xx.x)                                        | xx / xxx (xx.x)                                        |         |
|                              | ALT >5 x ULN and ≤10 x ULN  | xx / xxx (xx.x)                                        | xx / xxx (xx.x)                                        |         |
|                              | ALT >10 x ULN               | xx / xxx (xx.x)                                        | xx / xxx (xx.x)                                        |         |
| Day 3                        | ALT ≤1.5 x ULN              | xx / xxx (xx.x)                                        | xx / xxx (xx.x)                                        | 0.xxxx  |
|                              | ALT >1.5 x ULN and ≤3 x ULN | xx / xxx (xx.x)                                        | xx / xxx (xx.x)                                        |         |
|                              | ALT >3 x ULN and ≤5 x ULN   | xx / xxx (xx.x)                                        | xx / xxx (xx.x)                                        |         |
|                              | ALT >5 x ULN and ≤10 x ULN  | xx / xxx (xx.x)                                        | xx / xxx (xx.x)                                        |         |
|                              | ALT >10 x ULN               | xx / xxx (xx.x)                                        | xx / xxx (xx.x)                                        |         |
| Day 7                        | ...                         |                                                        |                                                        |         |
| Day 28                       | ...                         |                                                        |                                                        |         |
| Highest value post Day 0 ... |                             |                                                        |                                                        |         |

ULN = Upper limit of normal range

p-values from Chi-square test for the difference between PA and AL.

**Table 2.7.4-17**      **Incidence of AST values relative to the normal range, by treatment and time point**  
**Paediatric safety population**

*Programming note: Same layout as Table 2.7.4-16 for AST*

**Table 2.7.4-18**      **Incidence of liver enzyme classifications, by treatment and time point**  
**Paediatric safety population**  
**(Page 1 of n)**

| Time point                   |                                                     | Pyronaridine
artesunate
(N=xxx)
n / total (%) | Artemether
lumefantrine
(N=xxx)
n / total (%) | p-value |
|------------------------------|-----------------------------------------------------|--------------------------------------------------------|--------------------------------------------------------|---------|
| Day 0                        | ALT >3 x ULN                                        | xx / xxx (xx.x)                                        | xx / xxx (xx.x)                                        | 0.xxxx  |
|                              | ALT >5 x ULN                                        | xx / xxx (xx.x)                                        | xx / xxx (xx.x)                                        | 0.xxxx  |
|                              | ALT >10 x ULN                                       | xx / xxx (xx.x)                                        | xx / xxx (xx.x)                                        | 0.xxxx  |
|                              | AST >3 x ULN                                        | xx / xxx (xx.x)                                        | xx / xxx (xx.x)                                        | 0.xxxx  |
|                              | AST >5 x ULN                                        | xx / xxx (xx.x)                                        | xx / xxx (xx.x)                                        | 0.xxxx  |
|                              | AST >10 x ULN                                       | xx / xxx (xx.x)                                        | xx / xxx (xx.x)                                        | 0.xxxx  |
|                              | ALT or AST >3 x ULN                                 | xx / xxx (xx.x)                                        | xx / xxx (xx.x)                                        | 0.xxxx  |
|                              | ALT or AST >5 x ULN                                 | xx / xxx (xx.x)                                        | xx / xxx (xx.x)                                        | 0.xxxx  |
|                              | ALT or AST >10 x ULN                                | xx / xxx (xx.x)                                        | xx / xxx (xx.x)                                        | 0.xxxx  |
|                              | TBIL >1.5 x ULN                                     |                                                        |                                                        |         |
|                              | TBIL >2 x ULN                                       |                                                        |                                                        |         |
|                              | TBIL >3 x ULN                                       |                                                        |                                                        |         |
|                              | Hy's law (ALT or AST >3 x ULN
and TBIL >2 x ULN) |                                                        |                                                        |         |
| Day 3                        |                                                     |                                                        |                                                        |         |
| Day 7                        | ...                                                 |                                                        |                                                        |         |
| Day 28                       | ...                                                 |                                                        |                                                        |         |
| Highest value post Day 0 ... |                                                     |                                                        |                                                        |         |

ULN = Upper limit of normal range

TBIL = total bilirubin

p-value from Fisher's exact test for the difference between PA and AL.

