## 8. SAFETY ANALYSIS

### 8.1 Adverse events

The following adverse event summaries will be generated by treatment group.

- An overview of the number and percentage of patients with
  - any adverse event
  - any serious adverse event
  - any severe or life-threatening adverse event
  - any adverse event considered to be related to study drug, whereby related will be defined as possible, probable, definite, or missing relationship, as assessed by the investigator. If the relationship to study medication is missing the worst case will be assumed, i.e. such AEs will also be considered study drug related.
  - any serious adverse event considered to be related to study drug
  - any adverse event leading to death.
- Number and percentage of patients with adverse events by MedDRA primary system organ class and preferred term by treatment group
- Number and percentage of patients with study drug related adverse events (defined as possible, probable, definite or missing relationship to study drug) by MedDRA primary system organ class and preferred term by treatment group
- Number and percentage of patients with serious adverse events by MedDRA primary system organ class and preferred term by treatment group

- Number and percentage of patients with adverse events by MedDRA primary system organ class, preferred term and maximal severity, by treatment group

Listings of all serious adverse events will be provided.

The overview of AEs, AEs by primary system organ class and preferred term, AEs considered to be drug related by primary system organ class and preferred term, serious AEs and serious AEs considered to be drug-related will further be summarized by body weight category and treatment.

Potential differences between PA and AL in AE incidence rates will be analysed using Fisher's exact test.

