Scatter plots for ALT, total bilirubin showing individual data by day (y axis will present value, x-axis will present Day 0, 3, 7 and 28) – separately for treatment groups for all patients and for patients who had at least one re-treatment.

ALT classifications relative to the normal ranges, incidence rates of potential liver abnormalities and shifts of ALT categories will further be summarised by body weight category.

Potential differences between PA and AL of ALT and AST classifications relative to the normal ranges will be analysed using the Chi-square test and incidence rates of potential liver abnormalities using Fisher's exact test.

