| Preferred term 1             | xxx (xx.x)                 | xxx (xx.x)                 | 0.xxxx  |
| Preferred term 2             | xxx (xx.x)                 | xxx (xx.x)                 | 0.xxxx  |
| Primary system organ class 2 | xxx (xx.x)                 | xxx (xx.x)                 | 0.xxxx  |
| Preferred term 1             | xxx (xx.x)                 | xxx (xx.x)                 | 0.xxxx  |
| Preferred term 2             | xxx (xx.x)                 | xxx (xx.x)                 | 0.xxxx  |
| etc.                         |                            |                            |         |

A patient with more than one adverse event within a primary system organ class is counted only once for that class.  
p-values from Fisher's exact test for the difference between PA and AL.

**Table 2.7.4-7**      **Incidence of adverse events considered to be study drug related, by MedDRA primary system organ class and preferred term**  

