**Table 2.7.4-29**      **Overview of adverse events, by body weight category**  
**Paediatric safety population**  
**(Page 1 of 1)**

*Programming note: Same layout as Table 2.7.4-5. Present body weight categories <8 kg, 8-<15 kg and 15-<20 kg.*

**Table 2.7.4-30**      **Incidence of all adverse events by MedDRA primary system organ class and preferred term  
Paediatric safety population  
(Page 1 of n)**

*Programming note: Same layout as Table 2.7.4-6. Present body weight categories <8 kg, 8-<15 kg and 15-<20 kg.*

**Table 2.7.4-31**      **Incidence of adverse events considered to be study drug related, by MedDRA primary system organ class and  
preferred term, by body weight category  
Paediatric safety population**

*Programming note: Same layout as Table 2.7.4-30. Present only AEs that were considered to be study drug-related.*

**Table 2.7.4-32**      **Incidence of serious adverse events, by MedDRA primary system organ class and preferred term, by body weight  
category  
Paediatric safety population**

*Programming note: Same layout as Table 2.7.4-30. Present serious AEs.*

**Table 2.7.4-33**      **Incidence of serious adverse events considered to be study drug related, by MedDRA primary system organ class and  
preferred term, by body weight category  
Paediatric safety population**

*Programming note: Same layout as Table 2.7.4-30. Present serious AEs that were considered to be study drug related.*

**Table 2.7.4-34**      **Incidence of ALT values relative to the normal range by treatment and time point, by body weight category**  

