**Table 2.7.4-35**      **Incidence of liver enzyme classifications, by body weight category and time point**  
**Paediatric safety population**

*Programming note: Same layout as Table 2.7.4-18. Present body weight categories <8 kg, 8-<15 kg and 15-<20 kg.*

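### Rare AEs and liver abnormalities are compared by an unadjusted p-value per row with no between-group estimate or confidence interval, so non-significance can be misread as no difference

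*SAP*

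**What the plan says.** SAP Section 8.1 sets the comparison for adverse events: "Potential differences between PA and AL in AE incidence rates will be analysed using Fisher's exact test". Section 8.2 assigns a chi-square test to the ALT and AST classifications and sets the comparison of "incidence rates of potential liver abnormalities using Fisher's exact test".

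The shells in Section 12 follow this:

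- Table 2.7.4-5 (AE overview) has n, % and a p-value on six rows, with the footnote "p-values from Fisher's exact test for the difference between PA and AL". Table 2.7.4-6 has a p-value on every system organ class and preferred term row, and Tables 2.7.4-7 to 2.7.4-9 copy its layout.
- Table 2.7.4-18, titled "Incidence of liver enzyme classifications, by treatment and time point", lists liver criteria at Day 0, 3, 7 and 28 and for "Highest value post Day 0", with the footnote "p-value from Fisher's exact test for the difference between PA and AL".
- Table 2.7.4-35 repeats it by weight: "Same layout as Table 2.7.4-18. Present body weight categories <8 kg, 8-<15 kg and 15-<20 kg". Table 2.7.4-29 does the same for the AE overview: "Same layout as Table 2.7.4-5. Present body weight categories <8 kg, 8-<15 kg and 15-<20 kg".

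No section or shell contains a PA–AL difference, a ratio or a confidence interval. No significance level, multiplicity statement or rule for reading the p-values is given.

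**The concern.** The events of most interest in this pooled safety analysis, such as Hy's Law cases and ALT or AST >10 x ULN, are likely to be few. For few events, Fisher's p-value depends mainly on how many events there are. It can stay well above 0.05 while the data remain compatible with a material excess on one arm. Without an interval beside it, the reader cannot see how large an excess remains possible.

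The opposite error is also open. With hundreds of overlapping rows and no statement on how to read them, an isolated small p-value can be taken for a signal. Some rows cannot inform the question at all: Day 0 values are taken before dosing, so a p-value there cannot reflect an effect of either drug.

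**Working it through.** The SAP states no sample size, significance level or expected rate, so there is no planned figure to reproduce. The check has three parts: a count from the shells, exact calculations under assumed sizes, and an illustration of what an interval would add.

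**1. Number of liver p-values (from the shells)**

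- Criteria per time point in Table 2.7.4-18: ALT 3 + AST 3 + ALT or AST 3 + bilirubin 3 + Hy's Law 1 = 13.
- Time rows: Day 0, 3, 7, 28 and highest post Day 0 = 5.
- Table 2.7.4-18: 13 x 5 = 65 Fisher tests.
- Table 2.7.4-35: 65 x 3 weight categories = 195 Fisher tests.
- Tables 2.7.4-16, -17 and -34 (one chi-square per time row): 5 + 5 + 15 = 25.
- Total: 65 + 195 + 25 = 285, of which 260 are Fisher and 25 chi-square.
- At Day 0: 13 + 39 + 1 + 1 + 3 = 57.

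The p-value cells are blank in the shell for the three bilirubin rows and the Hy's Law row. Section 8.2 covers them, so they are counted: 4 x 5 x (1 + 3) = 80 of the 260. Leaving them out gives 180 Fisher tests.

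The AE overview adds 6 (Table 2.7.4-5) + 18 (Table 2.7.4-29) = 24. The system organ class and preferred term tables add a number not known in advance.

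**2. What Fisher's test can detect (sizes assumed, two-sided 0.05 assumed)**

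For x PA events and none on AL, the two-sided p-value sums the hypergeometric probabilities of all tables no more likely than the one observed. The smallest x giving p<0.05 is:

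| Assumed PA v AL | PA events needed | PA incidence | p |
|---|---|---|---|
| 500 v 330 | 7 | 7/500 = 1.4% | 0.046 |
| 400 v 200 | 9 | 9/400 = 2.3% | 0.033 |
| 60 v 30 (a small weight category) | 8 | 8/60 = 13% | 0.048 |

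For 3/400 v 0/200, the probabilities of 3, 1 and 0 of the three events falling on PA are about (2/3)^3 = 0.296, 3(2/3)(1/3)^2 = 0.222 and (1/3)^3 = 0.037. Two on PA (0.444) is more likely than the observed table and is left out. The sum is 0.555; the exact hypergeometric value is 0.554, so p = 0.55.

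The Clopper-Pearson 95% interval for 3/400 runs from the 0.025 quantile of Beta(3, 398) to the 0.975 quantile of Beta(4, 397): 0.15% to 2.2%.

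The threshold depends on direction. At the same 400 v 200, 0 PA against 3 AL events gives p = 0.037, about (1/3)^3.

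Exact power for true rates of 2% v 0.5%, by enumerating two binomials, is 1% at 200/100, 17% at 400/200, 37% at 600/300 and 54% at 800/400.

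**3. What an interval would add (counts assumed)**

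Take 8/400 PA v 1/200 AL. The planned row would show 2.0%, 0.5% and p = 0.28. The Wilson 95% limits are 1.02% to 3.90% for PA and 0.09% to 2.78% for AL. The Newcombe interval for the difference of 1.5 points is then:

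- lower: 1.5 − √[(2.00 − 1.02)² + (2.78 − 0.50)²] = 1.5 − 2.5 = −1.0
- upper: 1.5 + √[(3.90 − 2.00)² + (0.50 − 0.09)²] = 1.5 + 1.9 = +3.4

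The interval shows that an excess of more than 3 percentage points is not excluded; p = 0.28 does not show this.

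**The case against.** The strongest reply is that the p-values are only one part of the safety display. The SAP also plans n/total (%) per arm and visit, ALT and AST shift tables, plots of peak bilirubin against peak ALT and AST, individual plots over time, a maximal-severity table and a listing of serious events. A single patient meeting Hy's Law would be visible without any test. Since n and totals are printed, a reader could compute the crude difference and its interval. The wording about potential differences suits exploratory flagging.

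Most of this stands, and it rules out stronger readings that a reader might infer:

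- That non-significance will be taken as equal safety. The SAP sets no significance level or decision rule and nowhere equates p>0.05 with no difference. Only the possibility of misreading is supported.
- That safety is judged by p-values alone, or that the plan can support neither a signal nor reassurance. The other displays contradict this.
- That 285 is a count of separate hypotheses. The >3, >5 and >10 x ULN rows are nested, ALT and AST overlap with the combined criterion, and the visits feed the highest value.
- That Fisher's test needs a large imbalance in either direction. At 400 v 200, three AL events against none on PA are enough.
- That preferred-term p-values must go. That is preference.

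What the reply does not answer is that no planned output shows the precision of the PA–AL comparison, and that the p-values are neither labelled descriptive nor limited to post-dose data.

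**Conclusion.** The point holds as a gap in presentation and precision. No planned figure is shown to be wrong, and nothing in the SAP is contradicted. The gap lies in what this plan itself fixes, because it specifies the tests and draws the tables.

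The counts (285 liver p-values, 57 of them at Day 0) follow from the shells, given that Section 8.2 applies to the rows with blank cells. The event thresholds, power and example intervals rest on assumed sizes and counts; the 13% figure depends wholly on an assumed 60 v 30. They show how the method behaves and do not predict the results. This is an inexpensive improvement worth making before the tables are produced.

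**What to change.** 1. In Table 2.7.4-5 and the "Highest value post Day 0" rows of Table 2.7.4-18, add the PA–AL risk difference with a 95% CI. Name one method in advance, for example Miettinen-Nurminen stratified by study.
2. Use only studies that contribute both arms. Section 1 lists SP-C-003-05 Cohort D with PA patients only and names both arms explicitly only for SP-C-007-07, so the SAP should state which studies enter the difference. A footnote should say that Cohort D patients are in the pooled n (%) but not in the difference.
3. Add exact 95% CIs per arm for Hy's Law and for ALT/AST >5 and >10 x ULN.
4. Remove the p-values at Day 0.
5. State that the remaining p-values are unadjusted descriptive flags and that p>0.05 is not evidence of equal risk.

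The cost is edits to table shells and standard SAS output, with no new data. The downsides are slightly larger tables and a difference that will not exactly match the pooled percentages beside it. An interval and a Fisher p-value can also disagree near 0.05, which is a further reason to name the method in advance.

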**Table 2.7.4-19**      **Shift table of ALT categories from Day 0 pre dose to the worst post dose value, by treatment**  
**Paediatric safety population**  
**(Page 1 of n)**

| Treatment               |                | Number (%) of patients: Day 0 |            |                |              |               |            |
|-------------------------|----------------|-------------------------------|------------|----------------|--------------|---------------|------------|
|                         |                | Total                         | <1.5 x ULN | >1.5-<=3 x ULN | >3-<=5 x ULN | >5-<=10 x ULN | >10 x ULN  |
| Pyronaridine artesunate | Total          | xxx (100)                     | xxx (xx.x) | xxx (xx.x)     | xxx (xx.x)   | xxx (xx.x)    | xxx (xx.x) |
|                         | <1.5 x ULN     | xxx (xx.x)                    | xxx (xx.x) | xxx (xx.x)     | xxx (xx.x)   | xxx (xx.x)    | xxx (xx.x) |
|                         | >1.5-<=3 x ULN | xxx (xx.x)                    | xxx (xx.x) | xxx (xx.x)     | xxx (xx.x)   | xxx (xx.x)    | xxx (xx.x) |
|                         | >3-<=5 x ULN   | xxx (xx.x)                    | xxx (xx.x) | xxx (xx.x)     | xxx (xx.x)   | xxx (xx.x)    | xxx (xx.x) |
|                         | >5-<=10 x ULN  | xxx (xx.x)                    | xxx (xx.x) | xxx (xx.x)     | xxx (xx.x)   | xxx (xx.x)    | xxx (xx.x) |
|                         | >10 x ULN      | xxx (xx.x)                    | xxx (xx.x) | xxx (xx.x)     | xxx (xx.x)   | xxx (xx.x)    | xxx (xx.x) |
| Artemether lumefantrine | Total          | xxx (100)                     | xxx (xx.x) | xxx (xx.x)     | xxx (xx.x)   | xxx (xx.x)    | xxx (xx.x) |
|                         | <1.5 x ULN     | xxx (xx.x)                    | xxx (xx.x) | xxx (xx.x)     | xxx (xx.x)   | xxx (xx.x)    | xxx (xx.x) |
|                         | >1.5-<=3 x ULN | xxx (xx.x)                    | xxx (xx.x) | xxx (xx.x)     | xxx (xx.x)   | xxx (xx.x)    | xxx (xx.x) |
|                         | >3-<=5 x ULN   | xxx (xx.x)                    | xxx (xx.x) | xxx (xx.x)     | xxx (xx.x)   | xxx (xx.x)    | xxx (xx.x) |
|                         | >5-<=10 x ULN  | xxx (xx.x)                    | xxx (xx.x) | xxx (xx.x)     | xxx (xx.x)   | xxx (xx.x)    | xxx (xx.x) |
|                         | >10 x ULN      | xxx (xx.x)                    | xxx (xx.x) | xxx (xx.x)     | xxx (xx.x)   | xxx (xx.x)    | xxx (xx.x) |

ULN = upper limit of normal range

Patients with a pre-dose and at least on post dose ALT value are included.

**Table 2.7.4-20**      **Shift table of AST categories from Day 0 pre dose to the worst post dose value, by treatment  
Paediatric safety population**

*Programming note: Same layout as Table 2.7.4-19 for AST*

**Table 2.7.4-21**      **Summary of haemoglobin values (g/L) by treatment and time point  
Paediatric safety population**

*Programming note: Same layout as Table 2.7.4-11 for haemoglobin*

**Table 2.7.4-22**      **Summary of platelet values (10\*\*3/mm\*\*3) by treatment and time point  
Paediatric safety population**

*Programming note: Same layout as Table 2.7.4-11 for platelets*

**Table 2.7.4-23**      **Summary of white blood cell count values (10\*\*3/mm\*\*3) by treatment and time point  
Paediatric safety population**

*Programming note: Same layout as Table 2.7.4-11 for WBC*

**Table 2.7.4-24**      **Summary of absolute neutrophils (10\*\*3/mm\*\*3) by treatment and time point  
Paediatric safety population**

*Programming note: Same layout as Table 2.7.4-11 for absolute neutrophils*

**Table 2.7.4-25**      **Summary of absolute lymphocytes (10\*\*3/mm\*\*3) by treatment and time point  
Paediatric safety population**

*Programming note: Same layout as Table 2.7.4-11 for absolute lymphocytes*

**Table 2.7.4-26**      **Summary of absolute eosinophils (10\*\*3/mm\*\*3) by treatment and time point  
Paediatric safety population**

*Programming note: Same layout as Table 2.7.4-11 for absolute eosinophils*

